#### Measurement of RH-PAT

Peripheral endothelial function will be evaluated by performing RH-PAT using the Endo-PAT2000 device (Itamar Medical, Caesarea, Israel). The principles and measuring procedures of RH-PAT have been described in detail elsewhere [25, 26, 31]. In brief, measurements are performed in the morning at baseline and at 24 weeks, in a quiet, light- and temperature-controlled room, and when the examinee is in a fasted state and in a stable condition before taking their medication for the day. A BP cuff is placed on the upper arm and the opposite arm serves as a control. PAT probes are put on one finger of each hand. After at least a 15-min resting period on a bed in the supine position, the patient’s baseline pulse amplitude is recorded from each fingertip for 6 min. The cuff is subsequently inflated to 60 mmHg above systolic BP or 200 mmHg for 5 min. Finally, the pulse amplitude after cuff deflation is recorded for 5 min. The RHI is automatically calculated by a computerized algorithm in an operator-independent manner [25, 31]. At the same time, the augmentation index (AI) and heart rate variability (HRV), including the standard deviation of the normal to normal intervals (SDNN) and the ratio of low-to high-frequency (LF/HF) are also calculated automatically by using the Endo-PAT2000 software (above version 3.4.4).

### Trial endpoints

The primary endpoint in this trial is the change in RHI from baseline to 24 weeks. Secondary endpoints are baseline to 24 week changes in the following parameters and their correlation with the RHI: double product, calculated as heart rate × systolic BP; baPWV; coefficient of variation of the R–R intervals (including the differences between the results at rest and those during deep breathing) and the standard deviation of heartbeat intervals; LVEF and E/e’; specific biomarkers, including NT-proBNP, IL-8, hs-TnI, RAGEs, and ANGPTL2; renal function, including serum creatinine, eGFR, and creatinine-corrected urinary albumin excretion and L-FABP; glycemic parameters, including HbA1c, fasting blood glucose, and glycoalbumin; clinical parameters, including BP, pulse pressure (systolic BP minus diastolic BP), HR, BW, body mass index, and laboratory measures (details listed in Additional file 1); AI, SDNN, and LF:HF evaluated by the Endo-PAT2000.

### Safety

Throughout the study, safety will be reported for the intention-to-treat population by recording the serious adverse events (AEs) regardless of causal relationship to the trial drugs and protocol, and pre-defined adverse events of special interest (AESI) such as hepatic injury, decreased renal function, metabolic acidosis, ketoacidosis, diabetic ketoacidosis, and events involving lower limb amputation (details in Additional file 2). When the investigators confirm these AEs, their severity or grade, procedures conducted, outcomes, and relationship to the study drug will be assessed. Investigators will promptly report the incidence of AEs to the secretariat who will in turn promptly report to the principal investigator. The principal investigator must report expeditiously to Nippon Boehringer Ingelheim and the Data and Safety Monitoring Board (DSMB). The DSMB consists of an authorized endocrinologist and clinical epidemiologists with relevant expertise. Blinded to treatment allocation, the DSMB will independently evaluate safety during the trial and also assess the necessity for any revisions to the trial design and validate any decisions to continue the trial. If needed, the DSMB will make recommendations on safety issues to the principal investigator. Criteria governing withdrawal from the trial are listed in Table 2.

**Table 2 Tab2:** Discontinuation criteria

Severe hypoglycemia
Seriously poor glycemic control (HbA1c ≥10.0%)
Development of diabetic ketoacidosis
Serious dehydration requiring rehydration therapy
Considered inappropriate to continue the trial by investigators due to aggravation of primary disease or complications
Considered inappropriate to continue the trial by investigators due to adverse side effects of the trial drug
Considered inappropriate to continue the trial by investigators due to some other reasons
Participant withdrawal of consent

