### Randomization and blinding

Eligible and consenting participants will be randomized (1:1), in a double-blind manner to either receive empagliflozin (10 mg once daily) or a placebo treatment (once daily), using the web-based minimization dynamic allocation method balancing for HbA1c (<7.0 or ≥7.0%), age (<65 or ≥65 years), systolic blood pressure (BP) (<140 or ≥140 mmHg), and current smoking status (nonsmoker or smoker) at the time of screening [33, 34].

After randomization, patients, investigators, the sponsors, and other individuals involved with various aspects of the trial (e.g., including the conduct or data analysis) are to remain masked to group assignments until after the database is locked and prior to the statistical analysis. Only a predesignated study person will have access to the sealed randomization key codes that will allow unblinding under circumstances considered an emergency and when the identity of the trial drug must be revealed strictly to the investigator for the purpose of providing appropriate medical treatment due to serious adverse effects or ensuring the safety of a trial participant. If the key code for any patient is opened, the principal investigator must be informed immediately of the unblinding incident.

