### Statistical considerations

#### Sample size estimation

The possible mode of action of empagliflozin on endothelial function remains to be determined due to the current lack of available evidence. In the EMPA-REG OUTCOME trial, empagliflozin did not affect the incidence of major atherosclerotic macrovascular events such as myocardial infarction and stroke [10], providing results that were comparable to the CV safety trials investigating dipeptidyl peptidase-4 (DPP-4) inhibitors. Empagliflozin markedly reduced the predefined composite CV outcome and hospitalizations for heart failure, whereas the trials assessing DPP-4 inhibitors did not demonstrate such reductions [38–40]. Given these background results, we hypothesized that the putative pharmacological effects of empagliflozin on endothelial function would at least be equivalent to the effect of DPP-4 inhibitors. Therefore, the sample size in the present trial was calculated on the basis of detecting similar treatment effects on endothelial function via assessments of the RHI. Hashikata et al. [32] reported that 3 months of treatment with teneligliptin, a DPP-4 inhibitor, improved the mean (±standard deviation [SD]) RHI from 1.58 ± 0.47 to 2.01 ± 0.72 in patients with T2DM. Therefore, we expected the mean changes in the RHI from baseline would be 0.40 in the empagliflozin group and 0.06 in the placebo group after 24 weeks of treatment with an estimated the difference between groups of 0.34 ± 0.06. At an alpha level of 5% for a two-sided test, a sample size of 50 patients per arm was needed to provide a power of 80% for each comparison. Taking into consideration the possibility of an estimated 10% dropout rate, we estimated that 55 patients per arm (N = 110 patients) will be the appropriate sample size to provide sufficient statistical power for this trial.

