#### Statistical analysis plan

The analyses of the primary and secondary endpoints will be performed in the full analysis set, which includes all participants who received at least one dose of treatment during the trial period and who did not have any serious violation of the trial protocol, such as not providing informed consent or registration outside of the trial period.

Summary statistics will be used to calculate the baseline characteristics including the frequencies and proportions for categorical variables and mean ± SD for continuous variables. The patient characteristics will be compared using Chi square tests for categorical variables, t tests will be used for normally distributed continuous variables, and the Wilcoxon rank sum tests will be employed for continuous variables with a skewed distribution.

For the primary analysis—a comparison of treatment effects between the treatment groups—the baseline-adjusted means and their 95% confidence intervals will be estimated by analysis of covariance adjusted for the following allocation factors at the time of screening: HbA1c (<7.0 or ≥7.0%), age (<65 or ≥65 years), systolic BP (<140 or ≥140 mmHg), and current smoking status (nonsmoker or smoker). The primary analysis will not take missing observations into account and the mixed effects model for repeated measures (MMRM) will be used as a sensitivity analysis to examine the effect of missing data. In addition, MMRM will also be used as a sensitivity analysis to assess changes in the RHI during the trial period and be modelled as a function of time and treatment, and the treatment-by-time interaction will be evaluated. Subgroups for the analyses will be defined based on, but not limited to, the RHI at baseline (e.g., <2.0 or <1.67). A secondary analysis will be performed in the same manner as the primary analysis. In addition, correlations between the changes in the RHI and each measurement listed as a secondary endpoint will be evaluated using Pearson’s correlation coefficient.

The principal investigator and a biostatistician will develop the statistical analysis plan before completion of patient recruitment and database lock. All p values will be two-sided, and p values <0.05 will be considered statistically significant. All statistical analyses will be performed using SAS software version 9.4 (SAS Institute, Cary, NC, USA).

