### Trial organization and oversight (details in Additional file 3)

The principal investigator of the EMBLEM trial is [name] from the Department of Cardiovascular Medicine at Saga University. The research advisors are [name] from the Department of Clinical Pharmacology and Therapeutics at the University of the Ryukyus School of Medicine and [name] from the Department of Cardiovascular Regeneration and Medicine at the Research Institute for Radiation Biology and Medicine at Hiroshima University. The steering committee is involved in the planning, operational, analytical, and presentation aspects of the trial. The executive committee will supervise the design and operation of the trial. The roles of the DSMB are described in the section on safety. The trial secretariats are in the Department of Cardiovascular Medicine, Saga University and DOT WORLD CO., LTD., Tokyo, Japan. Data management, monitoring activities, statistical analyses, and audits will be implemented independently on the basis of an outsourcing agreement. The trial drugs, purchased from Boehringer Ingelheim, are to be stored appropriately at the Department of Pharmacy, Saga University Hospital, and will be shipped to each site in response to web-based participant registrations. Data monitoring will be enforced to ensure the research is performed properly, with an independent audit team inspecting several main institutes to ensure the quality of the trial data.

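### Safety is reported in the intention-to-treat population rather than in dosed participants by treatment received, which slightly dilutes any drug harm (minor)

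*Protocol article*

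**What the plan says.** The protocol article names two analysis populations.

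- **Safety section:** "safety will be reported for the intention-to-treat population", "by recording the serious adverse events (AEs) regardless of causal relationship to the trial drugs and protocol", together with predefined adverse events of special interest (AESI). The article does not define intention-to-treat anywhere, and it names no dosed or as-treated safety set.
- **Statistical analysis plan section:** "The analyses of the primary and secondary endpoints will be performed in the full analysis set", a set that "includes all participants who received at least one dose of treatment during the trial period" and that also drops participants with serious protocol violations. This dosing rule is not extended to safety.

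Two other places bear on the point. The Trial organization and oversight section says that the trial drugs "will be shipped to each site in response to web-based participant registrations". The Safety section also requires each event's relationship to the study drug to be assessed.

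**The concern.** Intention-to-treat suits a superiority comparison of efficacy because the dilution it brings is conservative there. For harm the same dilution works the other way and makes a drug look safer than it is. The article applies a dosing requirement to efficacy and omits it for safety, so the harm comparison rests on the wider set. A population is named, so this is a stated choice and not a detail left to a later document.

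Two kinds of patient matter:

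- A randomized patient who never takes study drug adds to the denominator but cannot show a drug effect. The required assessment of relationship to study drug also has no meaning for that patient.
- A patient who receives the other arm's kit is counted in the arm not taken, so drug events can be credited to placebo.

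The trial is small, and AESI such as ketoacidosis and amputation can be expected to be rare, so it is reasonable to ask how much signal would be lost.

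**Working it through.** The article gives no safety event rate, no number of never-dosed patients and no kit-error rate. There is therefore no figure of its own to reproduce, and the check sizes the dilution under stated assumptions.

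**Inputs from the article:** 55 patients per arm (Sample size estimation); 1:1 allocation (Randomization and blinding).

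**Assumptions:** u never-dosed patients in each arm; k kit swaps in each direction; true risk p1 on drug and p0 on placebo among the dosed.

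**Never-dosed patients.** If the undosed carry the background risk p0, the drug arm's observed risk is [(55 − u)·p1 + u·p0]/55 and the placebo arm's stays p0. If the undosed have no events, the two risks are (55 − u)·p1/55 and (55 − u)·p0/55. In both cases

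observed risk difference = (p1 − p0) × (55 − u)/55.

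| u per arm | share of risk difference kept |
|---|---|
| 1 | 54/55 = 98.2% |
| 2 | 53/55 = 96.4% |
| 3 | 52/55 = 94.5% |
| 5 | 50/55 = 90.9% |

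Each never-dosed patient per arm therefore costs 1/55 = 1.8%.

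**Swapped kits.** The observed risks are [(55 − k)·p1 + k·p0]/55 and [(55 − k)·p0 + k·p1]/55, so

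observed risk difference = (p1 − p0) × (1 − 2k/55).

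This keeps 96.4% for k = 1 and 92.7% for k = 2. Each pair costs 2/55 = 3.6%.

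**Risk ratio.** If the undosed have no events and are balanced, the factor (55 − u)/55 cancels and the ratio is unchanged. If they carry background risk, it moves toward 1: with 20% versus 5% and u = 5, from 4.0 to 3.73.

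**A worked case (rates assumed).** With 20% versus 5% and five never-dosed per arm, the risk difference falls from 15.0 to 15.0 × 50/55 = 13.6 points. Approximate power for a two-sided 5% comparison is 60% to 62% under intention-to-treat, and 62% in the 50 dosed per arm.

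Using dosed patients by treatment received restores the full risk difference in every case above.

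**The case against.** The strongest reply has four parts.

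1. **The label is undefined.** An analysis plan not shown could restrict intention-to-treat to dosed patients. That is possible, but the published sentence would then still need correcting, because its ordinary meaning is all randomized, as assigned.

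2. **No test of adverse events is specified.** The Statistical analysis plan section gives tests for baseline characteristics and efficacy only. Safety will probably rest on counts and listings, and intention-to-treat drops no event from these. This stands and limits the consequence.

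3. **Intention-to-treat has merits here.** It preserves the randomized comparison and retains patients whom the full analysis set removes for serious violations. This stands too, and any replacement set should also retain dosed violators.

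4. **Nothing shows that such patients exist.** The article reports no never-dosed patient and no kit error. This also stands.

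Three stronger readings are tempting, and the article does not support them.

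- **A few undosed patients could hide an imbalance.** They barely matter to a test: 6/55 versus 0/55 gives a two-sided Fisher p = 0.0271, and removing five undosed per arm (6/50 versus 0/50) gives p = 0.0267.
- **A single wrong kit could turn p = 0.027 into p = 0.21.** The contrast of 6/55 versus 0/55 with 5/55 versus 1/55 (p = 0.206) needs the misallocated drug-taker to be one of the six with an event, about 6/55 = 11%. Keeping 55 per arm on both bases also needs a swap; one error alone gives 6/56 versus 0/54 by treatment taken (p = 0.027). It is a selected worst case, not an expected effect.
- **Events before the first dose will be counted as on treatment.** The article says recording runs for the whole study but sets no counting window, and an analysis plan may set one. Shipping drug after registration makes a delay before first dose possible; it does not show how long the delay is or that anyone goes undosed.

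**Conclusion.** The point holds and is minor. The Safety section names a population that, read in its usual sense, biases a risk difference for harm toward no difference, while the dosing rule the article already contains is applied only to efficacy. The likely loss is a few percent of the risk difference, and reaches about 9% only if five patients per arm are never dosed.

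The result rests on the usual meaning of intention-to-treat, on assumed numbers of never-dosed and wrong-kit patients, and on similar numbers of never-dosed patients in the two arms, which is reasonable under blinding. The direction of the bias and the very low cost of correcting it are the reasons to act; the size alone would not be.

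**What to change.** In the Safety section, replace the intention-to-treat population with a safety set: all randomized participants who took at least one dose of study drug, including dosed participants excluded from the full analysis set for protocol violations, analysed by the treatment actually received. List any events before first dose separately. An intention-to-treat table can stay as a supplement.

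The cost is one sentence in the protocol or the analysis plan. The Measurements section already has trial medication recorded at each visit, so no new data item should be needed. The small downside is that safety denominators may differ from the number randomized, which a footnote to the safety table can explain.

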**Methods:**

The EMBLEM trial is an ongoing, prospective, multicenter, placebo-controlled double-blind randomized, investigator-initiated clinical trial in Japan. A total of 110 participants with T2DM (HbA1c range 6.0–10.0%) and with established CVD will be randomized (1:1) to receive either empagliflozin 10 mg once daily or a placebo. The primary endpoint of the trial is change in the reactive hyperemia (RH)-peripheral arterial tonometry-derived RH index at 24 weeks from baseline. For comparison of treatment effects between the treatment groups, the baseline-adjusted means and their 95% confidence intervals will be estimated by analysis of covariance adjusted for the following allocation factors: HbA1c (<7.0 or ≥7.0%), age (<65 or ≥65 years), systolic blood pressure (<140 or ≥140 mmHg), and current smoking status (nonsmoker or smoker). Key secondary endpoints include the change from baseline for other vascular-related markers such as arterial stiffness, sympathetic nervous activity, and parameters of cardiac and renal function. Importantly, serious adverse effects independently on the causal relationship to the trial drugs and protocol will be also evaluated throughout the trial period.

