### Treatment

All participants will be followed-up for 24 weeks. Although no specific glycemic target was set (e.g., HbA1c) in the present trial, all participants are to be treated in accordance with the treatment guidelines for T2DM and the official recommendations for appropriate use of SGLT2 inhibitors from the Japan Diabetes Society [35, 36]. Each participant’s pretrial or background glucose-lowering therapy is to remain unchanged during the trial if their medical condition is not compromised by such an approach. However, if participants in either treatment group cannot achieve their glycemic goal, the coadministration of glucose-lowering agents other than SGLT2 inhibitors, or increased dosages of the other glucose-lowering agents will be allowed, if the risk of developing hypoglycemia is minimized. If a patient’s blood glucose exceeds 13.3 mmol/L (>240 mg/dL) after an overnight fast, confirmed by a second measurement on different day, rescue medication can be initiated for the treatment of hyperglycemia. The initiation, choice, and dosage of rescue medication(s) are at the investigator’s discretion. Rescue medication can include an up-titration of a background treatment. If insulin is a background therapy, changes of >10% of the total daily prescribed-dose of insulin are considered rescue therapy. All rescue medication is to be taken in accordance with the prescribing information, with consideration given to minimizing the potential for contraindications and the risk for hypoglycemia. After the trial is completed, all participants can select any glucose-lowering treatments in accordance with their individual requirements.

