This trial has several limitations. First, it includes a relatively small sample size. Second, although the RH-PAT test is noninvasive, easy to perform, and an operator-independent method, its measurement is prone to be affected by individual physical conditions, intravascular volume, and the examination room environment. To minimize any such influences at participating institutions, investigators must perform the test in accordance with the EMBLEM-style operation manual which is modified from the manufacturer’s instruction (Additional file 4). In addition, because the empirical prediction implies that changes in the RHI in response to treatment may differ according to the RHI level, we plan to analyze data using subgroups stratified by the RHI level at baseline, as a subgroup analysis. Finally, SGLT2 inhibitors can potentially trigger some characteristic adverse drug reactions, such as intravascular volume depletion and urinary tract and genital infections, especially in the elderly and women [79]. Hence, investigators are cautioned to monitor patients for such reactions throughout the trial. In addition, information will be collected on predefined AESI as described earlier.

In summary, with the recent accumulation of evidence suggesting that SGLT2 inhibitors have CV and renal protective effects beyond glucose-lowering, the clinical use of SGLT2 inhibitors in patients with T2DM and established CVD could gain increased momentum.

Therefore, further assessments of the mechanisms that underpin the functionality of SGLT2 inhibitors are certainly warranted. The EMBLEM trial is the first study to assess the effect of empagliflozin on endothelial function in patients with T2DM and established CVD. In addition, possible mechanisms driving empagliflozin-mediated interactions between endothelial function and other CV markers will be evaluated. This trial has the potential to reveal profound mechanisms of action by which empagliflozin protects the CV system and improves CV outcomes in the EMPA-REG OUTCOME trial.

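### The adverse-event recording rule covers only serious events and pre-defined AESI, so non-serious events outside that list, including side effects that end participation, need not be captured or compared by arm

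*Protocol article*

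**What the plan says.** The Safety section of the protocol article sets the scope of safety reporting as "recording the serious adverse events (AEs) regardless of causal relationship to the trial drugs and protocol, and pre-defined adverse events of special interest (AESI". It illustrates the AESI with "such as hepatic injury, decreased renal function, metabolic acidosis, ketoacidosis, diabetic ketoacidosis, and events involving lower limb amputation (details in Additional file 2". Grading and causality then apply to that same set of events: "When the investigators confirm these AEs, their severity or grade, procedures conducted, outcomes, and relationship to the study drug will be assessed". The reporting line that follows runs from investigator to secretariat to principal investigator, and on to the drug company and the DSMB. The abstract is narrower still and mentions only that "serious adverse effects independently on the causal relationship to the trial drugs and protocol will be also evaluated throughout the trial period".

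Other sections name risks that this scope does not mention:

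- Treatment ties added glucose-lowering therapy to the risk of hypoglycemia, and asks that rescue medication be used "with consideration given to minimizing the potential for contraindications and the risk for hypoglycemia".
- Table 2 (Discontinuation criteria) includes severe hypoglycemia, "Serious dehydration requiring rehydration therapy", and "Considered inappropriate to continue the trial by investigators due to adverse side effects of the trial drug".
- The limitations paragraph of the Discussion names intravascular volume depletion and genital and urinary infections as characteristic reactions to the drug class, and says that "investigators are cautioned to monitor patients for such reactions throughout the trial". It then adds, as a further measure, that AESI information will be collected.
- Measurements provides an examination at each visit for genital or urinary infections requiring antibiotics.

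**The concern.** The article sets a rule for what is recorded, and that rule leaves no place for an event that is neither serious nor an AESI. A later analysis plan can choose how to tabulate data, but it cannot recover events that were never written down.

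Table 2 shows the problem most clearly. An investigator can judge that a side effect is due to the trial drug and is reason enough to end participation. If the event is neither serious nor an AESI, nothing in the article requires it to be recorded as an adverse event, graded, or reported.

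With 55 patients planned per arm and 24 weeks of treatment, serious events will probably be few. Non-serious events and withdrawals for side effects would then carry much of the tolerability comparison. The Discussion also says that the RH-PAT measurement can be affected by intravascular volume, so records of volume depletion would help a reader interpret the primary result, although they would not change its analysis.

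**Working it through.** The document gives no safety event rate, no share of events expected to be serious and no safety sample size, so there is no figure to reproduce. The check compares each named risk with the recording rule.

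| Risk, and where it is named | Must it be recorded under the Safety rule? |
|---|---|
| Severe hypoglycemia (Table 2) | Yes, if the episode meets the definition of serious |
| Non-serious hypoglycemia (Treatment names the risk in general) | Only if Additional file 2 lists it as an AESI |
| Serious dehydration needing rehydration (Table 2) | Yes, if it meets the definition of serious |
| Non-serious volume depletion (Discussion, limitations) | Only if Additional file 2 lists it; the text shown says to monitor |
| Side effects of the trial drug that end participation (Table 2, no seriousness threshold) | Only if serious or an AESI |
| Genital or urinary infections needing antibiotics (Measurements, Discussion) | Not through this rule unless serious or an AESI, but Measurements has them looked for at each visit |

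Three things follow.

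1. The row on side effects that end participation depends least on the unseen file. A longer AESI list would close that gap only if it included, as a category, AEs leading to discontinuation.
2. Hypoglycemia and volume depletion are not among the six printed AESI examples, and neither has its own recording rule in the article. The list is open, however, so their status is undetermined rather than excluded.
3. The article describes a visit-level examination for one named reaction (infections) and none for hypoglycemia or volume depletion. Measurements, Safety with Table 2, and the Discussion therefore treat the named risks unevenly.

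On size: if a share s of the relevant events is serious and none of the rest is an AESI, the share that need not be recorded is 1 − s. The document gives neither s nor the number of events, so s may lie anywhere from 0 to 1 and no magnitude follows.

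**The case against.** The strongest reply is that the article condenses a fuller protocol and refers the AESI detail to Additional file 2. The printed AESI are examples, so hypoglycemia or volume depletion may well be on the full list. This stands. A reader might infer from the printed examples that both have dropped out of the safety comparison, but the document does not show that.

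A reader might also take the Discussion to rely on the AESI list to capture the reactions it has just named. It does not: AESI collection is stated as an addition to the monitoring.

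Serious episodes of either kind are recorded whatever their cause. Blood pressure, heart rate and body weight are measured at baseline and at each visit, and renal function at baseline and 24 weeks. Their changes are secondary endpoints analyzed by arm, so hemodynamic, weight and renal signs related to volume depletion are compared. This also stands and narrows the point to clinical events that are not serious.

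Finally, it can be said that limiting collection to serious events and AESI is a deliberate choice in a small surrogate-endpoint trial, that nothing promises full AE collection, and that the reason for withdrawal is probably on a case report form in any case. The first two parts are fair. The third is plausible, but the article does not say so. A reason noted for withdrawal is also not the same as an event that is graded, sent to the DSMB and tabulated. A scope chosen on purpose can still fit poorly with the protocol's own discontinuation criteria.

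**Conclusion.** The point holds in a limited form. Under the rule as printed, non-serious AEs outside the AESI list need not be recorded, reported to the DSMB or compared by arm. That includes drug side effects that end participation under Table 2 and, unless Additional file 2 lists them, non-serious hypoglycemia and volume depletion.

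The conclusion assumes that the Safety section states the full recording rule and that the AEs passed along its reporting line are the ones it has just defined. For hypoglycemia and volume depletion it depends further on the content of Additional file 2. A claim that a given fraction of the safety signal is lost would rest on invented rates and is not made here. The primary endpoint, its analysis and the sample size are not touched. This is worth correcting because the change is cheap and data not collected cannot be restored afterwards.

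**What to change.** In the Safety section, extend the events that are recorded, sent to the DSMB and tabulated by arm to:

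- every AE, of any seriousness, that leads to stopping study drug or to withdrawal under Table 2;
- hypoglycemia, and volume depletion or dehydration, where Additional file 2 does not already cover them. If it does, say so in the Safety section.

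Reconcile Measurements, Safety (with Table 2) and the limitations paragraph of the Discussion, so that each named risk has a stated route into the data, and bring the abstract's safety sentence into line.

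The cost is a few extra form fields at the existing 4-, 12- and 24-week visits, a slightly longer safety table and modest extra reporting work for sites. The change concerns recording and reporting only. No treatment, rescue or discontinuation rule is altered.
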